Drawing on theories of network diffusion and social influence, and known patient-level, non-structural barriers (poor CC knowledge; stigma and misconceptions) and facilitators of CC screening (peer support and knowing someone who has screened), we developed the peer advocacy intervention *Game Changers for Cervical Cancer Prevention* (GC-CCP; R21TW011728) as a patient-level implementation strategy to increase CC screening. GC-CCP empowers women who have recently screened for CC to encourage screening among women in their social networks by disseminating CC knowledge, dispelling myths and fears and reducing CC stigma, and facilitating motivation for CC screening. In a pilot randomized controlled trial (RCT) of the peer-led, 7-session group intervention, 40 women who had screened for CC (index participants) were assigned to the intervention (n=20) or wait-list control (n=20), from whom 103 of their social network members (referred to as "alters") who had never screened for CC were enrolled; at month-6, 64% of intervention alters had been screened for CC, compared to just 16% of control alters [OR (95% CI)=12.13 (4.07, 36.16)]. Also, not only did GC-CCP significantly increase CC prevention advocacy among intervention index participants, alters of those in the intervention group (who had no exposure to the intervention, other than indirectly through advocacy from index participants) also reported increased engagement in CC prevention advocacy, compared to controls. The promising results of this pilot, and the strong track record of successful collaboration by our multidisciplinary study team (experts related to CC in the local context, implementation science (IS), and development and evaluation of the network-based peer advocacy intervention), positions this application to make a strong impact on CC prevention and control in Uganda, which could be generalizable to other LMIC settings.

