\* **Pilot of Game Changers for CC prevention (GC-CCP):** With an R21, we did formative research to adapt the GC model for CC. Focus groups with women who had and had not screened for CC revealed that like the HIV context, stigma, knowledge, and disclosure were key factors for engagement in advocacy, and thus retained in the intervention model. Internalized stigma did not appear to be an impediment to CC screening per se, but rather stigma and fear acted more as barriers to CC screening disclosure (especially if screened positive), and procedures related to VIA and treatment (e.g., misconceptions that such procedures would harm the vagina and make a woman sterile). A 7-session version of GC-CCP was developed and tested in an RCT with 40 screened women (20 intervention, 20 control) as index participants, from whom 103 alters (58 intervention, 45 control) who had never screened for CC were recruited; all participants were followed for 6 months (with 96% retention). The intervention was feasible and acceptable: peer facilitators were trained to implement the sessions, and 19/20 intervention index participants attended every session.

**Intervention effects on CC screening, CC prevention advocacy, and related outcomes.** In multivariate models controlling for baseline measures of the dependent variable and sociodemographics, alters in the intervention group were much more likely to have been screened for CC at month 6 [64% vs. 16%; adj. OR (95% CI) = 12.13 (4.07, 36.16)], and a higher percentage of alters named in the network assessments of the index survey (360 alters across all index participants; none of whom were perceived to have ever been screened at baseline) were perceived by the index to have been screened at month 6 [57% vs. 14%; adj. beta (SE) = 0.40 (.07);  $p<.001$ ], compared to those in the control. Index participants who perceived an enrolled alter to have screened for CC at month 6, were correct 88% of time. Alters in the intervention arm also reported greater engagement in CC prevention advocacy, CC knowledge, and CC risk management, compared to control alters (all  $p$  values < .001). Intervention index participants reported greater CC prevention advocacy at month 6, as well as greater sharing of CC screening experience, CC knowledge, CC prevention advocacy self-efficacy, and CC risk management (most  $p$  values < .001), compared to index participants in the control group.

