**Game Changers for CC Prevention (GC-CCP).** GC-CCP draws on theories of network diffusion, cognitive consistency, and social influence, which posit that behavior change can be initiated by a few and diffused to others through modeling, advocacy, and shifts in social norms. GC-CCP uses 7 sessions to empower CC screened women to act as change agents for CC screening in their social networks. **Session 1** addresses fears and concerns related to CC risk and use of self-compassion and peer support to overcome these fears. **Session 2** focuses on decision making for sharing one's personal CC screening experience, and how to initiate disclosure and conversations about CC. **Session 3** builds self-efficacy for CC risk management so that one's own behavior (e.g., recognizing signs of CC risk and seeking CC-related health services as needed; periodic VIA screens) coincides with the behavior they encourage in others, as well as learning CC facts and myths to facilitate accurate CC screening advocacy. **Session 4** demonstrates how one's social network can serve as a tool for dissemination of CC prevention advocacy and knowledge. **Sessions 5 and 6** build CC advocacy skills: communication skills (e.g., reflective listening, paraphrasing, open ended questions), and how to start and sustain conversations about CC. Participants learn to identify alters in their network who may be prime targets for advocacy and transfer of information and norms throughout the network (e.g., well connected to other alters; are "bridges" between two distinct groups of alters). **Session 7** inspires commitment to ongoing CC advocacy through peer solidarity and support. The 2-hour, weekly sessions will be conducted in Luganda using a structured manual, and group format to facilitate: sharing of experiences to build solidarity, support, and motivation among participants; group problem solving and role playing to build skills and self-efficacy; and homework between sessions to practice new skills and generate experiences to be processed in the sessions.

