**D2.2.1 Multi-site RCT of CC-CCP.** At all 4 sites, 40 women screened for CC in the past year will enroll as index participants (n=160), with 20 randomly assigned to the intervention, and 20 to a wait-list usual care control. Individual randomization entails contamination risks, but statistical models suggest  $\geq 30\%$  of the control arm must receive the equivalent of a full-strength intervention for meaningful contamination. We decided against an attention control, because attention paid to intervention (index) participants would not impact alter behavior (primary outcome), and its policy implications would be less clear. The intervention arm will be divided into 2 groups of 10 (balanced on ages 25-35 and 36+) for receipt of the intervention. The control arm receives the intervention after the 12-month follow-ups. Each index participant will recruit up to 3 alters (total= ~440 alters; referred to as 1st degree alters) with no history of CC screening. All index and 1st degree alter participants will be followed up at months 6 and 12. At month 6, 1st degree alters will recruit up to 2 of their own alters (2nd degree alters; total= ~800) who they report targeting with advocacy and thereafter getting screened for CC; 2nd degree alters will be administered a single, brief phone interview.

**Eligibility criteria:** *Index participants:* female, age 25+ (the lower limit for recommended CC screening), screened for CC in past year (clinic records), and no advanced stage disease (12-month follow-up is feasible). *1st degree alters:* female, age 25+, and report no CC screening history. *2nd degree alters:* female and age 25+.

**Recruitment** of index and 1st degree alters will span 8 weeks (5 index and 14 alters per week) at each site. Clinic staff will contact eligible women who have been screened for CC in the past year to inform them of the study; if interested, the site coordinator will perform consent processes and formal eligibility screening. Eligible women who enroll will complete the baseline survey, followed by randomization as an index participant.

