**1st degree alters:** The site coordinator will use the social network assessment within the baseline survey of each index to randomly select (using a random number table) 5 alters who know the participant's CC screening experience (or as many as there are if < 5) and ask the index if she is comfortable recruiting 3 of these alters. The index will be asked to call each selected alter at the end of their baseline interview to describe the study in the presence of the coordinator (or later in private, if she prefers), who will schedule a study visit for the alter. If an alter refuses or cannot be reached, a replacement will be randomly chosen from the original list of 5 alters.

**2nd degree alters:** The site coordinator will use the social network assessment in the month 6 survey of each 1st degree alter to randomly select 4 alters (or as many as there are if < 4) who the alter reports targeting with CC screening advocacy and thereafter was screened for CC. A similar process as described above for 1st degree alters, will be used to recruit and enroll 2nd degree alters. The coordinator will obtain verbal consent from the 2nd degree alter over the phone and the complete a brief 15-minute phone survey.

**Assessment schedule:** Surveys will be administered at baseline, month 6 and month 12 for index and 1st degree alters, and 2nd degree alters will be surveyed only once (at month 6 assessment of 1st degree alters). Participants will receive 30,000 Ush (~\$8) per assessment, except 2nd degree alters who will receive 10,000 Ush (via mobile money). To limit attrition, we will collect tracking information (phone numbers and mapped addresses), including contacts for family/friends with whom they have frequent contact. Clinic staff will help us track clients we have difficulty reaching. In the pilot, >96% of index and alters were retained at month 6.

**Measures:** Survey assessments for index and 1st degree alter participants will be interviewer-administered in Luganda using Network Canvas software, last ~ 75 minutes, and include a social network assessment. CC screening and treatment utilization will be verified with medical chart data.

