## Statistical Analysis

**Power:** Assuming 220 1st degree alters per arm enroll, 10% attrition (month 6 retention in pilot was 96%; we have retained 90-94% over 12 months in past studies in Uganda), ICC=.01-.05 range to control for clustering within the alters of each index participant, and a 15% CC screening rate in control alters (based on pilot data): the effective sample size will be 200 (ICC=.05) or 216 (ICC=.01) per arm. If ICC=.01, we will be able to detect a small effect size (11 percentage point difference) in alter CC screening at month 12 (80% power; alpha = .05). If ICC=.05, the detectable effect size is 12 percentage point difference (or odds ratio of 2.0).

**Aim 1:** *Assess effects of GC-CCP on alter CC screening.* We will use an intent-to-treat approach. In addition to comparing the arms at baseline and months 6 and 12, we will apply logistic generalized mixed models to our repeated-measures data to examine intervention effects, using a time by arm interaction to assess differences between the arms over time. We will account for correlation among participants in the same intervention group, and among alters referred by the same index, by adjusting standard errors for statistical inference tests with a sandwich estimator. We will use imputation for item nonresponse and attrition weights to account for non-random dropouts using logistic regression. We will control for and examine interaction effects with index (e.g., age), alter (e.g., knowledge of index's CC screening), and intervention (sessions completed) variables.

**Aim 2:** The analysis for this aim is described in the Preparation and Sustainment phases.

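### The Aim 1 intent-to-treat analysis is to control for sessions completed, a post-randomization variable that is zero for every control, so the adjusted arm contrast is not the intent-to-treat effect

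*Protocol*

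**What the plan says.** The Aim 1 paragraph (protocol, Statistical Analysis) opens with the principle: "We will use an intent-to-treat approach". It then plans two things: a comparison of the arms at baseline, month 6 and month 12, and a logistic mixed model for the repeated measures, "using a time by arm interaction to assess differences between the arms over time". The paragraph ends: "We will control for and examine interaction effects with index (e.g., age), alter (e.g., knowledge of index's CC screening), and intervention (sessions completed) variables". Sessions completed stands in one list with age, in the same role. Nothing confines it to a secondary or within-arm analysis.

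Three other places fix how this variable behaves:

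- Section D2.2.1, on the wait-list arm: "The control arm receives the intervention after the 12-month follow-ups".
- Section D.2.2, on the program: "GC-CCP uses 7 sessions to empower CC screened women to act as change agents for CC screening in their social networks".
- Section D.1, on pilot attendance: "19/20 intervention index participants attended every session".

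Section A describes the pilot alters in the intervention arm as women "who had no exposure to the intervention, other than indirectly through advocacy from index participants".

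**The concern.** An intent-to-treat contrast compares the arms as randomized. Covariates in that model should be fixed before randomization. Sessions completed is not: it measures adherence, it arises only in the intervention arm, and it lies on the route by which training the index woman is meant to change her alters' behavior. Conditioning on it answers a different question, namely what assignment does to the alters of a woman who attends nothing.

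At stake is the main effectiveness result. Followed literally, the model assigned to examine intervention effects could give an arm effect near zero, or one too imprecise to use, in a trial where the intervention works. It would then stand beside a simple arm comparison that says otherwise, with no stated rule for which one counts.

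**Working it through.** **The plan's own figures.** Power is stated for 220 alters per arm, 15% screening in controls and an ICC of .01 to .05. With design effect 1 + (m − 1) × ICC:

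- ICC .01, m = 2.75: 220 / 1.0175 = 216.2.
- ICC .05, m = 3: 220 / 1.10 = 200.0 (202.3 with m = 2.75).
- At 216 per arm, 15% vs 26% has 81.1% power (two-sided .05, sidedness assumed).

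These match the stated 216, 200 and 11 points, before any deduction for the stated 10% attrition. They presuppose an arm contrast whose variance is not inflated by another covariate.

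**Interaction.** Let A be arm (0 or 1) and S sessions completed. For controls A = 0 and S = 0. For intervention women A = 1, so A × S = S. The product column equals the sessions column in every row, so no separate interaction can be estimated.

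**Meaning of the arm term.** With b_A × A + b_S × S in the linear predictor, b_A is the arm difference at S = 0. On that scale the average contrast as randomized is b_A + b_S × m, where m is now mean sessions in the intervention arm. If the effect is proportional to sessions, b_A = 0 whatever the total effect.

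**Variance inflation.** With equal arms and S = 0 in controls, the between-arm variance of S is m²/4 and the pooled within-arm variance is v/2, where v is the variance of S in the intervention arm. Hence VIF = 1 + m²/(2v), and the standard error is multiplied by √VIF. Attendance in this trial is unknown, so four assumed patterns are shown. The last three take 76 of 80 at 7 sessions, from the pilot's 19/20. The first takes 5, 3, 3, 4, 5, 10, 20 and 50% at 0 to 7 sessions.

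| Attendance | m | v | VIF | SE multiplier |
|---|---|---|---|---|
| Moderate | 5.61 | 4.04 | 1 + 31.47/8.08 = 4.9 | 2.2 |
| 95% at 7, rest at 0 | 6.65 | 2.33 | 1 + 44.22/4.66 = 10.5 | 3.2 |
| 95% at 7, rest at 3 | 6.80 | 0.76 | 1 + 46.24/1.52 = 31.4 | 5.6 |
| 95% at 7, rest at 6 | 6.95 | 0.0475 | 1 + 48.30/0.095 = 509 | 22.6 |

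**Simulation.** Set-up: 80 index women per arm, 2 or 3 retained alters each, 15% vs 27% screened, ICC .05, logistic model, standard errors clustered on index. The true log-odds ratio is ln(.27/.73) − ln(.15/.85) = 0.74.

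- Sessions left out: median log-odds ratio 0.71 to 0.74, SE 0.26, power 81% to 84%.
- Sessions included, effect proportional to sessions: −0.03 (SE 0.58, rejection 6%) at moderate attendance; −0.15 (SE 4.7, rejection 9%) with 95% at 7 and the rest at 6.
- Sessions included, effect unrelated to sessions: 0.74 (SE 0.51, power 34%) at moderate attendance; 0.83 (SE 4.6, power 16%) with 95% at 7 and the rest at 6.

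**The named parameter, time by arm.** Moderate attendance, effect proportional to sessions, and 70% of screening done by month 6 (assumed):

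- Logistic model on months 6 and 12: the month-12 arm effect goes from 0.73 to −0.05 when sessions are added.
- Linear model with baseline rows: the month-12 time-by-arm term is 0.121 (83% rejection) without sessions. It is still 0.121 if sessions enter as a time-constant main effect, and −0.010 (7% rejection) if sessions vary with time.

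**The case against.** The strongest reply is that the protocol's effect parameter is the time-by-arm interaction, not a plain arm coefficient, and that one form of adjustment does no harm. If baseline rows are in the model and sessions enter only as a time-constant main effect, the interaction is unchanged. That is correct, and it limits the point. It is little protection here: 1st degree alters must report no screening history, so there are no baseline events, and this form is not practical in the planned logistic model.

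Second, a reader might infer that the trial is left without any intent-to-treat estimate. The documents do not support that. The same paragraph retains a comparison of the arms at months 6 and 12 and names no adjustment for it. What remains is that neither analysis is labelled primary, and the mixed model is the one assigned to examine intervention effects.

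Third, a reader might infer that adjustment always removes the effect, or quote a single inflation factor. Neither follows. Removal requires that the effect run through attendance; otherwise the loss is of precision only. The size rests on attendance that the documents do not give for this trial: 20 pilot women cannot settle it for four varied sites.

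Fourth, it is tempting to fault alter knowledge of the index's screening as well, since 1st degree alters are drawn from "alters who know the participant's CC screening experience" and sharing that experience is a candidate mediator. But the protocol does not say when this covariate is taken, and the human-subjects section allows recruitment of women outside the selected list, who may not know. No finding is made on it.

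Finally, the authors may have meant a dose-response analysis, and a statistical analysis plan that is not at hand may say so. The protocol's words, however, plan to control for the variable under a paragraph headed by intent-to-treat.

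**Conclusion.** The point holds. The Aim 1 text joins an intent-to-treat principle to an adjustment that is incompatible with it, and lists an arm-by-sessions interaction that cannot be estimated separately. Both follow from the protocol alone, because controls have no sessions until after month 12.

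The consequence is conditional. If the effect passes through the sessions, which is the mechanism the protocol describes, the adjusted month-6 and month-12 arm effect is about zero. If it does not, the estimate is roughly unbiased with a standard error about 2 to more than 20 times larger, depending on assumed attendance. The harmless form of adjustment and the retained arm comparison mean that a valid result is still obtainable, but the protocol does not direct the analyst to it.

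**What to change.** Restrict the intent-to-treat time-by-arm model to arm, time and pre-randomization covariates, for example site, index age and baseline alter characteristics. Delete sessions completed from the list of variables to control for and to test for interaction. Report it only as a labelled secondary dose or adherence analysis, such as dose-response within the intervention arm. State in the same place which Aim 1 analysis is primary.

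The cost is a sentence or two in the protocol, carried into the statistical analysis plan. Data collection, sample size and visits do not change.

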### **The specific aims are to:**

1. Conduct a multisite RCT of the GC-CCP network-based advocacy strategy to evaluate effects on CC screening uptake among unscreened alters across urban/rural and public/private clinics.
2. Use a mixed methods approach (semi-structured interviews and administrative clinic data) to examine clinic-, provider-, and client-level barriers and facilitators of GC-CCP Implementation and Sustainment.
3. Examine mediators and moderators (among index, alter and network characteristics) of intervention effects on (a) alter CC screening; and (b) engagement in CC prevention advocacy of index and alter (1st and 2nd degree) to better understand its multiplier effect on diffusion of advocacy throughout a network.
4. Evaluate the cost-effectiveness of Implementing GC-CCP to increase CC screening and low cost, early-stage treatment, and prevent advanced disease, compared to enhanced usual care.

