| CC internalized stigma                                                                                                              | 5 items; adapted from Kalichman                                     |
| CC enacted stigma                                                                                                                   | 6 items; adapted from Marlow & Wardle  and Cho et al.  |
| Extent of sharing of CC screening experience and result                                                                             | 3 items; dev. In-house; alpha=.74                                                |
| CC prevention advocacy self-efficacy                                                                                                | 3 items; dev. In-house; alpha=.85                                                |
| CC risk management self-efficacy (i.e., can identify signs of risk and seek help)                                                   | 3 items; dev. In-house; alpha=.64                                                |
| Covariates/Potential Moderators                                                                                              |                                                                                  |
| Background characteristics (age, education, income, relationship status, HIV status)                                                | Standard items                                                                   |
| General social support                                                                                                              | 4 items from MOS (Moser et al)                                      |
| Partner support for CC screening and treatment                                                                                      | 4 items; dev. In-house; alpha=.83                                                |

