**Aim 3:** *Examine mediators and moderators of the intervention effects on alter CC screening, and index and alter engagement in CC prevention advocacy.* Potential mediators consist of intervention mechanisms (sharing of CC screening experience, CC knowledge, CC risk management, CC prevention advocacy self-efficacy), while potential moderators include age, history of CC treatment, and network characteristics (e.g., % of alters who are trustworthy). We will explore interactions between a moderator and study arm to examine if the variable moderates the intervention effects. If categorical moderators are significant, we will conduct post-hoc simple main effects t-tests with Bonferroni corrections. For continuous moderators, we will graph significant interactions at low and high levels of each score ( $\pm 1$  SD) and conduct post-hoc simple main effects t-tests with Bonferroni correction by comparing differences between discrete points on the regression lines. To test for mediation, we will run regression models where: (a) the outcome is CC screening measured at month 12 and predictors are intervention indicator, a potential mediator measured at month 6, and covariates, if any; and (b) the outcome is the same potential mediator measured at month 6 and predictors are the intervention indicator and covariates, if any. We will apply a bootstrapping approach to the results from those two models to test whether mediators account for effects, using SAS Proc Causalmed.

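### The Aim 3 mediation model orders the survey visits but not the events: many alters will be screened before their month-6 mediator is measured, so for alter-level mediators a consequence of screening can be read as its cause

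*Protocol*

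**What the plan says.** The Aim 3 paragraph (Protocol, Statistical Analysis) sets out two regressions. In the first, "the outcome is CC screening measured at month 12 and predictors are intervention indicator, a potential mediator measured at month 6", plus covariates. In the second, "the outcome is the same potential mediator measured at month 6 and predictors are the intervention indicator and covariates, if any". The two are combined by bootstrap. Neither excludes, dates or adjusts for screening that took place before month 6.

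The mediators are named: "Potential mediators consist of intervention mechanisms (sharing of CC screening experience, CC knowledge, CC risk management, CC prevention advocacy self-efficacy". The specific aims leave open whose values these are: "Examine mediators and moderators (among index, alter and network characteristics) of intervention effects". The measures table in Section D2.2.1 lists among the potential mediators "Extent of sharing of CC screening experience and result", without saying that it applies to index women only.

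Four other places fix the timing:
- First-degree alters are eligible only if they report no screening history (Section D2.2.1).
- Training takes 7 weekly sessions (strategy specification table, Section D.2.2).
- Surveys take place at baseline, month 6 and month 12 (Section D2.2.1, assessment schedule).
- Pilot result: "at month-6, 64% of intervention alters had been screened for CC, compared to just 16% of control alters" (Section A; also Section D.1).

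**The concern.** A mediator at month 6 and an outcome at month 12 look correctly ordered. The order holds for the visits only. An alter screened in month 3 counts as screened at month 12, and her mediator was measured three months after her screening. If screening changed that mediator, the regression attributes the association to the mediator acting on screening.

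The reverse path is plausible for several named mediators when they are measured in the alter. A screening visit can teach a woman about cervical cancer and make her more confident in managing her risk. She can share a screening experience of her own only after having one. The pilot does not separate the directions: "Alters in the intervention arm also reported greater engagement in CC prevention advocacy, CC knowledge, and CC risk management, compared to control alters", and this was reported at the same month-6 visit as the higher screening.

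At stake is the part of Aim 3 that explains how the intervention raises alter screening. A false mechanism there would misdirect anyone who uses the result to decide which parts of the training matter.

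**Working it through.** The plan states no figure for the mediation analysis, so there is none to reproduce.

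**Inputs.** 220 alters per arm less 10% attrition (Statistical Analysis, Power): 220 × 0.9 = 198. Pilot screening by month 6: 64% and 16%. Planning scenario at month 12: 15% in controls and a detectable difference of 12 points, so 27% versus 15% (Power). Two assumptions do not come from the protocol: how screening is spread between months 6 and 12, and how far screening shifts the mediator.

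**Step 1. Is month-12 screening cumulative?** The protocol does not use the word. It is the natural reading: alters start unscreened, Table 2 defines effectiveness as the proportion of previously unscreened alters who get screened, and Section B gives a 3-year screening interval, so few repeat screens would fall in months 6 to 12. Counting only months 6 to 12 would not rescue the model, because early screeners would stay in it as non-events with post-screening mediator values.

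**Step 2. How much screening precedes the mediator?**
- Pilot rates: 198 × 0.64 = 127 intervention and 198 × 0.16 = 32 control alters.
- Share of intervention-arm month-12 screening already done: 0.64/0.70 = 91% if month 12 reaches 70%, 0.64/0.80 = 80% if it reaches 80%, and 64% if every alter is screened.
- Constant hazard at pilot rates: month 12 = 1 − (1 − 0.64)² = 87% and 1 − (1 − 0.16)² = 29%. Shares are 0.64/0.87 = 74% and 0.16/0.294 = 54%.
- Constant hazard at 27%/15%: month 6 = 1 − √0.73 = 14.6% and 1 − √0.85 = 7.8%. Shares are 54% and 52%.

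**Step 3. What does the planned model then report?** Simulated with 198 per arm, no clustering, and no effect of the mediator on screening:

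mediator = δ × (screened by month 6) + γ × arm + N(0,1)

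The arm-to-mediator path comes from the second regression and the mediator-to-screening path from the first. Mediation is declared when both have |z| > 1.96, which stands in for the planned bootstrap. The table gives the share of trials declaring mediation at δ = 0.5. Ranges span repeat runs, which include a logistic outcome model.

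| Screening rates | γ = 0 (mediator moves only through screening) | γ = 0.5 (training also moves it) |
|---|---|---|
| Pilot, constant hazard | 41–46% | 67% |
| Pilot, none after month 6 | 62–66% | 99–100% |
| 27%/15%, constant hazard | 3–4% | 52–57% |
| 27%/15%, none after month 6 | 7–9% | about 97% |

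With δ = 0 the rate is 0 to 6% in every row.

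**Step 4. How large is the false indirect effect?** At pilot rates it averages 0.011 to 0.035 under constant hazard, against a total difference of 0.87 − 0.29 = 0.58 (2 to 6%). With no screening after month 6 it is 0.021 to 0.065 against 0.48 (4 to 14%). At 27%/15%, against 0.12, it is 0.001 to 0.004 for γ = 0 (1 to 3%) and 0.022 to 0.044 for γ = 0.5 (18 to 37%).

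**Step 5. What does restricting the outcome do?** Among alters unscreened at month 6, with screening after month 6 as the outcome, the mediator-to-screening path is significant in 4 to 6% of runs wherever screening continues. At pilot rates (198 − 127) + (198 − 32) = 71 + 166 = 237 of 396 alters remain. If nobody is screened after month 6, nothing can be estimated.

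**The case against.** **The mediators may be the index's.** The framework and session content describe sharing, self-efficacy and advocacy skill as processes trained in index women, and alters are reached only through them. An alter's screening can hardly alter the index's score as it would her own. This stands for index-level mediators. But the aims name alter characteristics too, and the alter survey covers knowledge and risk management, so alter-level mediation is within scope. A reader might infer that the plan enters the alter's own sharing score; the protocol neither says so nor rules it out.

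**The error rates rest on assumptions.** This stands. The 0.5 SD shift has no source in the protocol. At 27%/15% with the mediator moving only through screening, false mediation is near or below 9%. The high rates need pilot-size uptake or a training effect on the mediator as well.

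**A lag is better than a same-visit analysis, and covariates are left open.** Both true. But baseline adjustment, which the open covariates permit, does not restore event order, and the text fixes outcome and mediator timing. This is therefore a stated choice, not a detail left to a statistical analysis plan.

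**Restricting to later screening can erase real mediation.** This is the strongest point. It conditions on an event after randomisation that removes 64% of one arm and 16% of the other at pilot rates. With true mediation, no reverse effect and about 63%/17% screened by month 6, the planned model found the mediation in 83 to 99% of simulated trials and the restricted one in 7 to 46%. The arm effect on the mediator shrank, for example from 0.50 SD to 0.29 or 0.20. The restricted analysis should therefore be added beside the planned model and should not replace it.

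**Conclusion.** The concern holds for alter-level mediators. The planned model does not secure time order, and at pilot rates about 127 of 198 intervention alters would have the outcome before the mediator is measured. Whether this yields a false mechanism depends on whether screening changes the mediator. At an assumed 0.5 SD, false mediation ranges from 3% to nearly every trial, according to uptake, its timing and any direct training effect on the mediator.

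A reader might go further and infer that Aim 3 will mistake effect for cause, or that most of the reported mediation would be artefact. The protocol does not support either. It gives no figure for the reverse effect, and the false share in the simulations is 2 to 14% at pilot rates, larger (18 to 37%) only at 27%/15% with a training effect on the mediator. Nor does the point reach the trial's main result: the Aim 1 comparison uses no mediator. It should be corrected before Aim 3 is analysed.

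**What to change.** Three changes to the Aim 3 text:

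1. Adjust both mediation models for the baseline value of the mediator, where it is collected. This removes prior differences between women; it does not by itself settle direction.
2. Take the sharing-of-experience score from the index, not from the alter whose screening is the outcome.
3. Keep the planned model, and add an analysis of first screening dated after the month-6 assessment, using chart and survey dates, among alters unscreened at month 6. Claim an alter-level mechanism only if the two agree.

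The cost is wording and some analysis time. Surveys and chart abstraction are already planned, though the abstraction must capture screening dates. State the downside in the plan: the added analysis uses a subset selected after randomisation (about 237 of 396 alters at pilot rates), has low power for real mediation, and cannot be estimated if little screening follows month 6. In that case report alter-level mediation as an association whose direction is unresolved.
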